# Analysis

### Outcome Definitions

The primary outcome is time in days to liberation from mechanical ventilation. Liberation from mechanical ventilation is defined to occur on the second of two consecutive ICU-days without the need for either IV or NIV. Liberation from mechanical ventilation was also considered to occur on the day of ICU discharge if cessation of mechanical ventilation occurs on the same day as ICU-discharge in patients that are not readmitted to the ICU within two days. The competing risk of death is said to occur if patients died before or within 24 hours from liberation from mechanical ventilation. Patients are censored if they were moved to a different hospital while still receiving mechanical ventilation or at 30 days if still receiving mechanical ventilation.

Secondary outcomes are the risk of death from any cause at 30 days, PaO2/FiO2-ratio (PAF-ratio) on the first day of ICU-admission and last measured PAF-ratio in patients dying within 5 days from inclusion.

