### Analysis Methods

The effect of sTM, Syndecan-1 and PECAM-1 on the primary outcome is analysed using cox regression and reported as cause-specific hazards using the method of Ozenne et al.^21^ A separate model is fitted for each of the explanatory variables of interest and each model is controlled for the abovementioned variables.

The effect of the markers of endothelial damage on the risk of death from any cause at 30 days is modelled with cox regression and controlled for the same variables as the analysis of the primary outcome.

We model the effects of continuous variables with restricted cubic splines with 2 knots^22^ if the introduction of splines significantly improves model fit as evaluated by the Wald Statistic.

The effect of the markers of endothelial damage on the PAF-ratio on the first day of ICU-admission and on last PAF-ratio in patients dying within 5 days of inclusion is modelled with linear regression and controlled for COPD, age, respiratory infection and shock (defined as need for vasopressor and a lactate >= 2).

All models will be examined for standard measures of model fit and assumptions and the included variables will be transformed as appropriately. We test for biological plausible interactions such as between levels of the biomarkers of endothelial damage and septic shock or respiratory infection. Interaction terms will be kept in the model if they are significant in the multivariable analysis based on the p-value for the effect of the interaction term.

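### Discharge from the ICU on the day after ventilation stops meets neither liberation rule and neither censoring rule, so the primary outcome has no valid coding for a successful course

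*SAP*

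**What the plan says.** The SAP itself defines the event, the competing event and the censoring, all under Outcome Definitions.

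- **Scale:** "The primary outcome is time in days to liberation from mechanical ventilation".
- **Rule 1, in the ICU:** liberation is "defined to occur on the second of two consecutive ICU-days without the need for either IV or NIV".
- **Rule 2, at discharge:** liberation also falls on the day of ICU discharge, but only "if cessation of mechanical ventilation occurs on the same day as ICU-discharge in patients that are not readmitted to the ICU within two days".
- **Competing event:** "The competing risk of death is said to occur if patients died before or within 24 hours from liberation from mechanical ventilation".
- **Censoring:** "Patients are censored if they were moved to a different hospital while still receiving mechanical ventilation or at 30 days if still receiving mechanical ventilation".

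Under Analysis Methods the primary outcome "is analysed using cox regression and reported as cause-specific hazards". Under Missing Data, an outcome with less than 2.5% missing is handled by case deletion, and one with more than 2.5% missing by multiple imputation. Under Outcome Assessment, ICU data are collected for 30 days and deaths for one year.

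**The concern.** Rule 2 exists because discharge can cut short the two ICU-days that rule 1 needs. It covers only one of the two ways in which that can happen. Someone who stops ventilation and leaves on the same day is liberated. Someone who stops, is watched in the ICU for one more day and then leaves is not, although that patient was seen breathing without support for longer.

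Such a patient has no event, no competing event and no censoring date. The programmer must then choose a coding that the plan does not give. The patient could be held at risk to day 30, censored at discharge, or treated as missing and so deleted or imputed, although the course is known. If the patient dies on the ward within follow-up, the wording makes this a death before liberation. The choice falls on the primary outcome, and the codings do not give the same hazard ratio.

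**Working it through.** **Step 1. Apply the rules to each exit day.** Let X be the last day with IV or NIV and k the ICU discharge day minus X. Assume a live discharge and no readmission within two days.

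| k | Cessation = last ventilated day; discharge day counts as an ICU-day | Same, but discharge day does not count | Cessation = first ventilation-free day; discharge day counts |
|---|---|---|---|
| 0 | event (rule 2) | event (rule 2) | no status |
| 1 | **no status** | **no status** | event (rule 2) |
| 2 | event (rule 1) | **no status** | event (rule 1) |
| 3 or more | event (rule 1) | event (rule 1) | event (rule 1) |

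The SAP defines neither cessation nor ICU-day. The first column is the plain reading. The other two move or widen the hole, and none closes it. Neither censoring clause helps: one needs a transfer during ventilation and the other applies only "at 30 days if still receiving mechanical ventilation".

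**Step 2. What a coding choice does to the hazard ratio.** The SAP gives no event count, effect size or frequency, so there is no figure to reproduce and every input here is an assumption. Let g_low and g_high be the shares of liberations on the uncovered course in low- and high-marker patients. Censoring them at discharge thins each group's liberation hazard by (1 − g), so approximately

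observed HR = true HR × (1 − g_high) / (1 − g_low).

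- Equal shares of 30%: 0.60 × 0.70/0.70 = 0.60.
- 15% low, 5% high: 0.80 × 0.95/0.85 = 0.89.
- 40% low, 20% high: 0.60 × 0.80/0.60 = 0.80.
- 20% low, 40% high: 0.60 × 0.60/0.80 = 0.45.

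**Step 3. Simulation.** The top marker quarter was compared with the rest: 60,000 patients per scenario, daily liberation hazard 0.15 in the reference group, daily death hazard 0.02 against 0.04, end at day 30, Cox model with Efron ties and no covariates.

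| True HR | g_low / g_high | Counted as liberated | Censored at discharge | Held to day 30 |
|---|---|---|---|---|
| 0.6 | 30% / 30% | 0.59 | 0.60 | 0.72 |
| 0.6 | 40% / 20% | 0.58 | 0.78 | 1.12 |
| 0.6 | 15% / 5% | 0.57 | 0.67 | 0.84 |
| 0.6 | 20% / 40% | 0.61 | 0.45 | 0.45 |
| 0.8 | 10% / 10% | 0.78 | 0.78 | 0.81 |
| 0.8 | 30% / 30% | 0.79 | 0.77 | 0.87 |
| 0.8 | 40% / 20% | 0.79 | 1.06 | 1.36 |
| 0.8 | 15% / 5% | 0.78 | 0.88 | 1.04 |
| 0.8 | 20% / 40% | 0.78 | 0.58 | 0.52 |

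The spread in the counted-as-liberated column (0.57–0.61 and 0.77–0.79) shows how much is simulation noise and whole-day rounding.

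**Step 4. Dropping these patients.** A second simulation used a continuous marker: daily liberation hazard 0.22, daily death hazard 0.03 with HR 1.35 per SD, 15–30% on this course, and odds of the course falling by a factor of 1.0–1.8 per SD. Dropping the patients gave 0.75–0.80 for a true 0.80 per SD, so the estimate was unchanged or moved slightly away from 1.

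**Step 5. Precision.** Where the HR is unchanged, events are still lost. With a share g the standard error grows by about 1/√(1 − g): 1/√0.90 = 1.05 for 10%, and 1/√0.70 = 1.20 for 30%.

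**The case against.** The strongest reply is that the plan prescribes no wrong coding. It leaves one narrow course without a status, and a sensible analyst would count these patients as liberated. All results are declared exploratory, and no sample size rests on the rule. The simulated shares are assumed, and the simulations ignore the planned adjustment for PAF-ratio, septic shock, kidney injury and other covariates, which could weaken any link between marker and early discharge.

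Much of this stands as a limit on size. A reader might infer three stronger things that the document does not support.

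- **That the course is common.** The SAP gives no frequency.
- **That the hazard ratio is pulled towards or past 1.** That needs the course to be more frequent in low-marker patients, or the patients to be held at risk to day 30. Holding them to day 30 is only one possible coding, because the day-30 clause covers only patients who are still ventilated. Other combinations leave the estimate alone or move it away from 1.
- **That discharge on X+1 is the only course lost, or that the best outcomes are removed.** Which exit day is lost depends on two undefined terms, and on the plain reading same-day leavers do count as liberated.

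What does not stand is the view that this is mere detail. Applied exactly, the stated rules deny an event to a known success and turn a later ward death into a competing event. The exploratory label concerns power and multiplicity. It does not supply an outcome for these patients.

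**Conclusion.** The defect is in the text and needs no assumption: on every reading tested, at least one successful exit day has no event and no censoring rule. Its effect on the primary hazard ratio cannot be sized from the SAP. Under assumed shares it ranges from almost nothing (10% in each group, censored at discharge: 0.78 for a true 0.80) to a change of side (15% against 5%, held to day 30: 1.04 for a true 0.80). With 20% against 40% it moves away from 1 (0.58 if censored at discharge). No direction of bias can be claimed. What can be claimed is that an unstated coding choice may decide the estimate, and that events are lost under any choice other than counting these patients as liberated. The rule should be settled before the primary analysis is run.

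**What to change.** Amend Outcome Definitions in four places.

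1. **Extend the discharge rule.** Suggested text: *Liberation is also considered to occur on the day of ICU discharge in any patient discharged alive from the ICU without IV or NIV before completing two ventilation-free ICU-days, provided the patient is not readmitted to the ICU within two days.* Same-day leavers keep their present date, and those who leave on X+1 are dated X+1.
2. **Define the terms.** State that cessation means the last day with IV or NIV, and whether the discharge day counts as an ICU-day.
3. **Add a censoring rule** for patients moved to another hospital off ventilation before liberation is met. The present rule covers only those moved while ventilated.
4. **Report the number** of patients whose outcome rests on the extended rule, preferably by marker group.

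The cost is a few sentences and a small change to the derivation. The current rules already need ICU discharge and readmission dates, and deaths are followed for a year. The downside is that ventilation on the ward after discharge is seen only through readmission, as under the current discharge rule. A definition based on two ventilation-free days wherever they are spent would avoid that, but it would re-date same-day leavers and need ward ventilation data that the SAP does not show to be collected.

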### Variables

The explanatory variables of interest are sTM, Syndecan-1 and PECAM-1. These are continuous and presented in ng/ml. They will also be introduced to the regression models as categorical variables divided into three groups: =< 25^th^ percentile, > 25^th^ and =< 75^th^ percentile, > 75^th^ percentile

To be controlled for in the multivariable analyses are the following known predictors of poor outcomes in the ICU: Gender, Age, A history of Chronic Inflammatory Pulmonary Disease (COPD), Septic Shock at ICU-admission, A history of Heart Failure, Worst PAF-ratio on the first day of ICU-admission, The presence of Respiratory Infection at ICU-admission, Acute Kidney Injury during the first day of ICU-admission and highest Bilirubin during first day of ICU-admission.

Septic shock is defined in accordance with the “Third international consensus definition for sepsis” as suspected or confirmed infection plus the need of vasoactive medication to maintain a mean arterial blood pressure of 65 and a blood lactate of 2 or more.^18^

COPD, Heart Failure and Acute Respiratory Infection are adjudicated by one author ([name]) based on information from the EMR without knowledge of the results of the primary outcome or of the values of sTM, Syndecan-1 or PECAM-1.

PAF-ratio is calculated with information from the EMR as the values of PaO2 and FiO2 giving the lowest ratio on a given day of ICU-admission.

Acute Kidney Injury is defined as stage 2 or more from the KDIGO guidelines and calculated based on the worst creatinine during the first day of ICU-admission.^19^ Baseline creatinine is defined as the median of all creatinine levels from 180 to 8 days prior to ICU-admission. In patients without a baseline creatinine, the creatinine levels is estimated with revised Lund-Malmö formula assuming a normal GFR of 70 ml/min/1,73m2.^20^

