# Introduction

### Background and Rationale

Acute respiratory failure is a common reason for admission to the Intensive Care Unit (ICU), and it is estimated that 13-20 million patients are mechanically ventilated worldwide annually^1^ with more than a third dying during the hospital admission, although studies suggest that the mortality have improved in recent years.^2–45^

Endothelial dysfunction has been proposed as a plausible link between critical illness and multiorgan failure^6^ and two Danish Randomized Controlled Trials (RCT) are currently testing the prostacyclin analogue Ilomedin as a targeted treatment against endotheliopathy in trauma and septic shock.

In experimental models, pathologic stimuli to the pulmonary endothelium results in the inflammation and noncardiogenic pulmonary oedema that are hallmarks of ARDS.^7–9^

In ARDS increased permeability of the intercellular connections between endothelial cells leads to fluid accumulating in the alveoli. A yet unpublished study found that Platelet Endothelial Cell Adhesion Molecule (PECAM-1) is the best marker for this interruption of the cell-cell junctions between the endothelial cells.

In clinical studies, soluble thrombomodulin (sTM) and Syndecan-1 are valid markers of damage to the profound endothelium and endothelial glycocalyx, respectively.^10^ In critically ill patients, both markers increase with more severe disease and predicts liver and renal failure.^10,11^ Increased sTM levels are associated to fewer ventilator free days,^12^ organ failure^13,14^ and mortality^14^ in patients with ARDS.

Syndecan-1 associates with acute respiratory failure in patients with pulmonary sepsis^15^ and severe sepsis after resuscitation with large volumes of fluids.^16^ Nevertheless, surprisingly both markers correlates poorly with hypoxaemia at ICU admission and need for mechanical ventilation.^10^

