# Trial Population

### Screening data

The ICU at Copenhagen University Hospital – North Zealand, Copenhagen, Denmark is a 12 bed, mixed surgical/medical ICU with around 900 admissions per year.

Between November 2016 and June 2019 all patients presenting to the ICU were screened for inclusion in the Metabolomics Study.

Unfortunately, no screening log was kept at the time.

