### Eligibility

The inclusion criteria consisted of age > 18, acutely admitted to the ICU and a presumed stay > 24 h. The exclusion criteria were non-obtainable informed consent or active treatment deemed futile by the treating clinician.

Included patients had study blood samples drawn daily for the first 5 days of their ICU-stay or until death or discharge, whichever came first.

For the present study in the Metabolomics cohort, only patients that presented with acute respiratory failure are included. Acute respiratory failure is defined as patients receiving either Invasive (IV) or Non-Invasive Ventilation (NIV) on the first day of ICU-admission.

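### Septic shock is the only shock term in the liberation and 30-day mortality models, so non-septic shock is coded with no shock, although the PAF-ratio models adjust for shock of any cause

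*SAP*

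**What the plan says.** - **Covariate list.** SAP, Variables, names nine covariates for the multivariable analyses. The list includes "Septic Shock at ICU-admission, A history of Heart Failure", and no other shock term. The remaining covariates are gender, age, COPD, worst first-day PAF-ratio, respiratory infection, first-day acute kidney injury (AKI) and highest first-day bilirubin.
- **Definition.** The definition of septic shock in the same section reads: "suspected or confirmed infection plus the need of vasoactive medication to maintain a mean arterial blood pressure of 65 and a blood lactate of 2", with higher lactate values included.
- **Where the list is used.** In Analysis Methods, the liberation analysis has one model per marker, and "each model is controlled for the abovementioned variables". The 30-day mortality model is "controlled for the same variables as the analysis of the primary outcome".
- **The PAF-ratio models.** Also in Analysis Methods, these are "controlled for COPD, age, respiratory infection and shock (defined as need for vasopressor and a lactate >= 2", with no mention of infection.
- **Who can be in the cohort.** Eligibility asks for patients "acutely admitted to the ICU and a presumed stay > 24 h", and for this substudy ventilation on the first ICU day. Infection is not required. Screening data describes a "12 bed, mixed surgical/medical ICU".
- **Interaction.** Analysis Methods gives marker by septic shock as an example of the interactions to be tested, and keeps a term if it is significant.

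**The concern.** A patient without infection who needs a vasopressor and has a lactate of 2 or more counts as shocked in the PAF-ratio models. In the two Cox models the same patient falls in the reference level of the shock covariate. The SAP gives no reason for the difference.

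This matters if non-septic shock is related to both the marker and the outcome. On the marker side, Background and Rationale says that sTM and Syndecan-1 increase with more severe disease, and it reports trials of a "targeted treatment against endotheliopathy in trauma and septic shock", so endotheliopathy is not seen as confined to sepsis. On the outcome side, the SAP already treats septic shock as a known predictor of poor outcome. If shock without infection also slows liberation and raises mortality, part of its effect would be credited to the marker, in the direction of the study's hypothesis.

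The example interaction is affected too. Septic shock would be contrasted with a group that mixes unshocked patients and patients in other forms of shock.

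**Working it through.** **1. Coding under the SAP's own definitions** (vasopressor need and lactate of 2 or more, with or without infection)

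| Patient | Cox models (liberation, 30-day death) | PAF-ratio models |
|---|---|---|
| Criteria met, infection | septic shock | shock |
| Criteria met, no infection | reference level | shock |
| Criteria not met | reference level | no shock |

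The second row is the issue. It follows from the text alone and needs no assumption.

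**2. Size: inputs.** The SAP gives no sample size, event count, share of non-septic shock, marker distribution or shock effect. There is no figure of its own to reproduce, and every input below is an assumption.

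- p, share of patients in non-septic shock: 0.05 to 0.20
- d, marker difference in those patients: 0.3 to 0.8 SD
- hazard ratio (HR) of shock: 0.6 for liberation, 2 for death
- true marker HR: 1.00

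**3. Size: approximation for an omitted binary confounder.**

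Spurious log HR per SD = s × ln(HR of shock), where s = p(1−p)d / (1 + p(1−p)d²).

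- p = 0.05, d = 0.3: s = 0.01425 / 1.0043 = 0.014. Liberation exp(0.014 × ln 0.6) = 0.993; death exp(0.014 × ln 2) = 1.010.
- p = 0.10, d = 0.5: s = 0.045 / 1.0225 = 0.044. Liberation 0.978; death 1.031.
- p = 0.20, d = 0.8: s = 0.128 / 1.1024 = 0.116. Liberation 0.942; death 1.084.
- The last case with shock HRs of 0.4 and 3: 0.899 and 1.136.

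**4. Size: simulation.** Cox models were fitted to 200,000 simulated patients in each of 27 scenarios, with a null marker and censoring at 30 days. Assumptions: 25% septic shock; 5%, 10% or 20% non-septic shock; marker shift of 0.3, 0.6 or 1.0 SD in any shock; shock HR 0.5 or 0.7 (liberation) or 2.0 (death).

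| Non-septic shock | Liberation HR per SD, septic-only term | Death HR per SD, septic-only term |
|---|---|---|
| 5% | 0.968 to 0.996 | 1.008 to 1.025 |
| 10% | 0.939 to 0.991 | 1.015 to 1.043 |
| 20% | 0.915 to 0.982 | 1.026 to 1.080 |

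With any-cause shock as the covariate, the marker HR was 0.996 to 1.003 throughout. That return to 1 is built in, because shock was the only confounder simulated. The simulation confirms the mechanism and its direction, not the size in this cohort. It also used one baseline rate (0.08 per day) for both events and no competing event, so the figures are rough.

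**5. What both calculations omit.** Neither includes AKI, bilirubin, PAF-ratio or heart failure history. These are in the SAP's models and would carry part of the shock effect, so each figure is nearer an upper value for its scenario.

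**The case against.** The strongest reply is that the plan already adjusts for severity. One might infer from the shock definition that the Cox models leave non-infected patients' severity unadjusted. They do not: septic shock is one of nine covariates, and first-day AKI, bilirubin, PAF-ratio and history of heart failure plausibly carry part of the same information. This stands and reduces the size. It does not remove the point, because none of the four measures current circulatory failure, and heart failure enters as a history.

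A reader might also infer that the SAP contradicts itself. It does not. The PAF-ratio models have a different outcome and a shorter covariate list, and lists may differ between outcomes. The two definitions show only that the finer coding is within reach.

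Nor does the SAP support a firm claim of bias for all three markers. Its statement on severity covers sTM and Syndecan-1 but not PECAM-1. It names trauma beside septic shock but says nothing about other causes of shock, and a mixed unit makes non-septic shock possible without saying how common it is. The extremes of 0.90 and 1.14 need every assumption at its limit and no absorption by other covariates.

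Septic shock against all others is a legitimate contrast if the question is specific to sepsis. The results are also declared exploratory, which lowers the stakes but does not remove bias.

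One objection fails. Shock might be called a mediator that should not be adjusted for, but the plan already adjusts for septic shock, and that argument would not justify treating other shock differently.

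**Conclusion.** The coding gap is certain. In the liberation and 30-day mortality models, eligible ventilated patients in non-septic shock share the reference level with unshocked patients.

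The consequence is conditional. Residual confounding is plausible for sTM and Syndecan-1, probably towards slower liberation and higher mortality; for PECAM-1 the SAP gives no basis for a direction. The actual size cannot be known from the SAP. Under the assumptions of the approximation it is small to moderate: about 0.94 to 0.99 per SD for liberation and 1.01 to 1.08 for death, with a middle case near 0.98 and 1.03. The simulation, which allows a larger marker shift and a stronger shock effect on liberation, reaches 0.915 for liberation and 1.080 for death. These are upper values for each scenario, because the other covariates were left out.

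This is a cheap improvement to the covariate definition. It is not an error that invalidates the models.

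**What to change.** In SAP, Variables, replace the septic shock covariate with a three-level one: no shock, non-septic shock, septic shock. Build it from the vasopressor and lactate definition in Analysis Methods plus infection status at admission, which Baseline Patient Characteristics lists as collected. Use it in the liberation model, the 30-day mortality model and the planned marker-by-shock interaction. The septic level is kept, so the septic-shock interaction remains testable.

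State one at-admission window for all levels. The shock definition in Analysis Methods gives no window, and the two definitions are worded differently: the one in Variables names a blood pressure target and the other does not. The same wording should apply to both shock levels.

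The cost is one extra parameter per model and a slightly wider interval, plus one more interaction term per marker where the interaction is fitted. Vasopressor use and lactate are already needed for the existing definitions, so no new data are required. If the non-septic level proves too sparse to fit, keep the septic shock term and report a sensitivity analysis with any-cause shock.

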### Objectives

The broader aim of the study is to expand the knowledge on the connection between endothelial dysfunction and patient-important outcomes in the setting of critically ill patients with acute respiratory failure. If a connection between the duration of mechanical ventilation and endothelial dysfunction is found it could lead to better prognostication and identification of the sickest patients at ICU-admission. This could pave the way for clinical trials testing a targeted treatment against the endotheliopathy to shorten the time that mechanical ventilation is required.

The objective of the study is to estimate the impact of endothelial dysfunction as measured with sTM, Syndecan-1 and PECAM-1 on the time to liberation from mechanical ventilation in a general ICU population admitted with acute respiratory failure.

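### The liberation and 30-day mortality models adjust for day-1 PAF-ratio, AKI and bilirubin, which may lie on the path from marker to outcome, and no adjusted model without them is planned

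*SAP*

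**What the plan says.** The SAP's Objectives section sets the target: "The objective of the study is to estimate the impact of endothelial dysfunction as measured with sTM, Syndecan-1 and PECAM-1 on the time to liberation". It does not say whether a total or a direct effect is meant. The same section names a prognostic use: "it could lead to better prognostication and identification of the sickest patients at ICU-admission".

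The covariates are listed under Variables and were chosen because they predict poor ICU outcomes. They include "Worst PAF-ratio on the first day of ICU-admission, The presence of Respiratory Infection at ICU-admission, Acute Kidney Injury during the first day of ICU-admission". Liver function enters the same list as "highest Bilirubin during first day of ICU-admission". Under Analysis Methods this set enters each of the three marker models for liberation, and the same set enters the models for 30-day death.

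Outcome Definitions also makes first-day PAF-ratio a secondary outcome, and Analysis Methods plans to model "The effect of the markers of endothelial damage on the PAF-ratio on the first day of ICU-admission" by linear regression. Variables defines PAF-ratio as the lowest ratio of the day, so outcome and covariate are the same quantity.

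Background and Rationale gives the mechanism: "Endothelial dysfunction has been proposed as a plausible link between critical illness and multiorgan failure". Of sTM and Syndecan-1 it says that "both markers increase with more severe disease and predicts liver and renal failure". It describes leakier endothelial junctions letting fluid into the alveoli, and presents PECAM-1 as the marker of that process.

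**The concern.** The plan selects covariates by whether they predict the outcome. That rule cannot separate a confounder, which precedes the marker and should be adjusted for, from a mediator, which carries part of the marker's effect. Each marker has at least one suggested route through an adjusted variable: gas exchange for PECAM-1, kidney and liver for sTM and Syndecan-1.

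If impact means the total effect, holding day-1 lung, kidney and liver function fixed removes whatever part of it runs through those organs. The Objectives section looks ahead to trials of an endothelium-directed treatment meant to shorten ventilation. A hazard ratio near 1 from the fully adjusted model could then be read as no impact when it shows only little association beyond day-1 organ dysfunction.

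Nothing else in the plan fills the gap. Statistical Principles promises univariable results where relevant, but these control for nothing, not even age or COPD. No liberation or mortality model adjusts for confounders while leaving the possible mediators out.

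**Working it through.** The SAP gives no sample size, event count or effect size, so there is no figure of its own to reproduce. The check has two parts.

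**1. What the text says of each variable**

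| Day-1 covariate | Place relative to the markers in the SAP |
|---|---|
| Worst PAF-ratio | Explicitly modelled as an outcome of the markers (Outcome Definitions, Analysis Methods) |
| AKI | Renal failure is predicted by sTM and Syndecan-1 (Background); nothing said for PECAM-1 |
| Highest bilirubin | Liver failure is predicted by sTM and Syndecan-1 (Background); nothing said for PECAM-1 |

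Only PAF-ratio is treated outright as something the markers affect. For the other two the word is prediction. Eligibility describes daily samples for up to five days, but no section says which sample enters the models, so its order relative to a worst-of-day value cannot be established.

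**2. How much adjustment could matter**

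Liberation was simulated with death as a competing event and censoring at 30 days, 20,000 patients per scenario, one seed. Every coefficient is an assumption:

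- marker scaled to SD 1, loading 0.3 on one baseline confounder;
- baseline hazards 0.12 per day for liberation and 0.02 per day for death;
- log hazard ratios for liberation: 0.35 per unit of PAF-ratio, −0.5 for AKI, −0.15 per unit of bilirubin, −0.15 for the confounder;
- direct marker log hazard ratio −0.2, so exp(−0.2) = 0.82, except under full mediation, where it is 0;
- marker effects on PAF-ratio / logit AKI / bilirubin: modest −0.2 / 0.4 / 0.24; strong and full −0.5 / 0.8 / 0.48; organ path only 0 / 0.6 / 0.36.

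The logic is: total log hazard ratio ≈ direct + sum of (marker effect on mediator × mediator effect on liberation). For modest mediation:

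- PAF-ratio: −0.2 × 0.35 = −0.070
- bilirubin: 0.24 × −0.15 = −0.036
- AKI, with intercept −1.4: p = 1/(1 + e^1.4) = 0.198, and 0.198 × 0.802 × 0.4 × −0.5 = −0.032
- total ≈ −0.2 − 0.070 − 0.036 − 0.032 = −0.338, hazard ratio about 0.71

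The reduced Cox fit gave 0.744. It lies nearer 1 because a Cox hazard ratio shrinks when strong predictors are left out; the no-mediation row shows the same (0.839 against 0.82).

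Share kept = ln(full HR) / ln(reduced HR). For modest mediation, ln 0.820 / ln 0.744 = −0.198 / −0.296 = 67%.

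| Scenario | Reduced HR (confounder only) | Full HR (plus three day-1 variables) | Share kept |
|---|---|---|---|
| No mediation | 0.839 | 0.818 | 114% |
| Organ path only, none through PAF-ratio | 0.763 | 0.817 | 75% |
| Modest mediation | 0.744 | 0.820 | 67% |
| Strong mediation | 0.644 | 0.815 | 46% |
| Full mediation | 0.759 | 1.001 | about 0% |
| No mediation, unmeasured severity drives marker and day-1 physiology | 0.748 | 0.832 | 63% |
| Mediation and unmeasured severity | 0.627 | 0.812 | 45% |

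In the row with severity but no mediation, the simulated conditional hazard ratio is 0.82. The full model (0.83) is close to it and the reduced model (0.75) exaggerates. A drop from reduced to full therefore does not by itself show mediation: modest mediation keeps 67% and pure severity confounding keeps 63%, and data alone would hardly tell them apart.

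**The case against.** The case for the planned model is substantial. A variable can be the outcome of one regression and a covariate in another, so listing PAF-ratio in both places is not a contradiction. The covariates are measures of acute severity, the background says the markers rise with severity, and Baseline Patient Characteristics lists PAF-ratio as baseline physiology. If severity drives both marker and outcome, leaving these variables out biases the estimate away from 1. For the prognostic aim, adjusting for day-1 organ dysfunction is the natural choice. The background also reports that sTM and Syndecan-1 correlate poorly with hypoxaemia, so a path through PAF-ratio may be small for those two; the remark does not cover PECAM-1. Finally, univariable results are promised and all results are called exploratory.

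Most of this stands. It shows that the full model is legitimate and that a reduced model should not simply replace it. It does not show that the full model alone answers the stated objective. The univariable results do not close the gap, because they mix mediation with every confounder. The exploratory label is tied to the missing power calculation and the absence of multiplicity correction; it does not settle which effect is estimated.

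**Conclusion.** The point holds as a gap in labelling and in the set of models. If impact means a total effect, the planned hazard ratios for liberation and 30-day death may be attenuated by an unknown amount: none without mediation, and to the null only with full mediation. Between these, 46% to 75% of the log hazard ratio was kept in the simulated mediation scenarios without severity confounding. Those shares rest wholly on assumed coefficients and apply to liberation; mortality was not simulated.

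A reader might infer that the plan adjusts the effect away, or that its hazard ratios must be pulled towards 1. The documents support neither. Full mediation is stated nowhere, only PAF-ratio is explicitly treated as an effect of the markers, and the order of sample and covariates is not given. A reader might also infer that the full model should be demoted. That is a choice between two risks, over-adjustment and residual confounding, and the SAP gives no ground for settling it one way.

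**What to change.** - Keep the planned model. Beside it pre-specify, for each marker and for both liberation and 30-day death, a model adjusted only for factors that precede the marker: age, gender, COPD, heart failure and respiratory infection at admission.
- Justify septic shock in the reduced model, or show results with and without it. Its definition in Variables rests partly on vasoactive need and lactate, so it is partly acute physiology.
- Label the reduced model 'total association' and the planned one 'association beyond day-1 organ dysfunction', and report them side by side.
- State which blood sample enters the models.
- State that a conclusion of no impact will not be drawn from the fully adjusted model alone.

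The cost is SAP wording and one extra model per marker and outcome, 3 × 2 = 6, with more fits if the percentile-group coding and the septic shock variant are repeated. Two adjusted estimates must then be explained, and the reduced one remains open to residual confounding by acute severity, which the report should say.
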